#### *Study centers*

The identification and the inclusion of the index case, as well as the pre and post visit counseling for genetic test will be performed by study centers. Study centers will be located in university or peripheral clinics specialized in lipid management. Clinicians involved in the study will be selected based on their expertise to manage lipid abnormalities and are all aware of the genetic characteristics of FH (see *below*). In addition, these clinicians will be trained on how to inform patients about the consequences of genetic tests for themselves and for their families. Study center who will include children are trained to perform blood test in children and to take care of adolescent according to best-medical practice, with well-trained nursing team.

#### *Restitution of genetic information*

FH is an autosomal dominant genetic disease. This means that

- the mutated gene is on a non-sexual chromosome (not the X or Y chromosome).
- the presence of a single mutated gene is enough for the disease to develop.

In practice this leads to the following characteristics:

- the disease affects both men and women

- each member of the family has 50% probability of receiving the genetic mutation

This non-complex mode of inheritance does not require advanced genetic knowledge to counsel families. Therefore, this information will be provided to patients by the physician of the study center. An additional consultation with a geneticist is not required. In case of doubt before the result is given to the patient, the interpretation of identified variants can be discussed with the biologist [name] in Sion.

Genetic analysis will be in charge of the investigator only if shipment of tubes are addressed to the central laboratory accredited for the Study. Similarly, for relatives of an index case with a monogenic mutation for FH, genetic analysis will be in charge of the investigator only if shipment of tubes are addressed to the same central laboratory accredited for the Study.

### *Study duration*

The study duration and the number of visit for each participant will differ according to the protocol (**Table 1**):

**Table 1:** study duration for each participant

| Participant                                                          | Study duration in months | Number of study visits overall | Number of mandatory one-site study visit |
|----------------------------------------------------------------------|--------------------------|--------------------------------|------------------------------------------|
| Index case                                                           | 8                        | 3                              | 1                                        |
| Relative of a monogenic postive FH with postive genetic test  | 7                        | 3                              | 1                                        |
| Relative of a monogenic postive FH with negative genetic test | 1                        | 2                              | 1                                        |
| Relative of a monogenic negative FH with postive lipid test   | 6                        | 2                              | 1                                        |
| Relative of a monogenic negative FH with negative lipid test  | 0                        | 1                              | 1                                        |

The inclusion of the 154 index cases is planned over 30 months (**Table 2**). The inclusion of the about 350 relatives is planned over 42 months. The time allowed to complete the three cycles of identification using cascade screening among families will be 12 months.

A 6-month follow-up visit will be performed for each of the 154 index cases, as well as for all relatives with a positive genetic or lipid test.

The total study duration will be 4 years: planned 06/2020 of First-Participant-In, planned 12/2024 of Last-Participant-Out.

**Table 2 :** Overall study duration

| Year                       | 2020 | 2021 | 2022 | 2023 | 2024 |
|----------------------------|------|------|------|------|------|
| Recruitment of index cases |      |      |      |      |      |
| Visits of index cases      |      |      |      |      |      |
| Inclusion of relatives     |      |      |      |      |      |
| Visits of relatives        |      |      |      |      |      |

The schedule of assessments for each type of participant is described in **Table 3a-c**

**Table 3a-c: schedule of assessments**

a) **Table 3a:** Schedule of assessments for index cases

| Time (months)                         | >-1            | 0              | +3                   | +9                   |
|---------------------------------------|----------------|----------------|----------------------|----------------------|
| Visit window (weeks)                  | ± 4            | 0              | ± 4                  | ± 4                  |
| Visit (see Figure 2)                  | Screening (V0) | Inclusion (V1) | Index case (V2)      | Follow-up (V2F)      |
| Type of contact                       | Letter         | On site        | On site or telephone | On site or telephone |
| Written patient information           | +              | +              |                      |                      |
| Oral and written patient information  |                | +              |                      |                      |
| Written consent                       |                | +              |                      |                      |
| Inclusion-/exclusion criteria         |                | +              |                      |                      |
| eCRF                                  |                | +              | +                    | +                    |
| Intervention                          |                |                | +                    |                      |
| Self-reported questionnaire baseline  |                | +              |                      |                      |
| Self-reported questionnaire follow-up |                |                |                      | +                    |
| Physical examination                  |                | +              |                      |                      |
| Genetic test                          |                | +              |                      |                      |
| Laboratory documentation              |                | +              |                      | +                    |
| Qualitative research (sample)         |                |                |                      | +                    |

See Appendix 1 for collected variables in each questionnaire/eCRF

b) **Table 3b:** Schedule of assessments for relatives of the monogenic positive FH group

| Time (months)                        | 0                        | +2                       | +8                                                            |
|--------------------------------------|--------------------------|--------------------------|---------------------------------------------------------------|
| Visit window (weeks)                 | 0                        | ± 4                      | ± 4                                                           |
| Visit (see Figure 2)                 | Cascade (V3 or V5 or V7) | Cascade (V4 or V6 or V8) | Follow-up only if genetic criteria for FH (V4F or V6F or V8F) |
| Type of contact                      | On site                  | On site or telephone     | On site or telephone                                          |
| Oral and written patient information | +                        |                          |                                                               |
| Written consent                      | +                        |                          |                                                               |
| Inclusion-/exclusion criteria        | +                        |                          |                                                               |
| Intervention                         |                          | +                        |                                                               |
| eCRF                                 | +                        | +                        | +                                                             |
| Self-reported questionnaire baseline | +                        |                          |                                                               |

|                                       |   |  |   |
|---------------------------------------|---|--|---|
| Self-reported questionnaire follow-up |   |  | + |
| Physical examination                  | + |  |   |
| Genetic test                          | + |  |   |
| Laboratory documentation              | + |  | + |
| Qualitative research (sample)         |   |  | + |

See Appendix 1 for collected variables in each questionnaire/eCRF

c) **Table 3c:** Schedule of assessments for relatives of the monogenic negative FH group

| Time (months)                         | 0                                             | +6                                                             |
|---------------------------------------|-----------------------------------------------|----------------------------------------------------------------|
| Visit window (weeks)                  | 0                                             | ± 4                                                            |
| Visit (see Figure 2)                  | Cascade (V3 or V5 or V7)                      | Follow-up only if clinical criteria for FH (V3F or V5F or V7F) |
| Type of contact                       | On site, by telephone if on site not possible | On site or telephone                                           |
| Oral and written patient information  | +                                             |                                                                |
| Written consent                       | +                                             |                                                                |
| Inclusion-/exclusion criteria         | +                                             |                                                                |
| eCRF                                  | +                                             | +                                                              |
| Intervention                          | +                                             |                                                                |
| Self-reported questionnaire baseline  | +                                             |                                                                |
| Self-reported questionnaire follow-up |                                               | +                                                              |
| Physical examination                  | +                                             |                                                                |
| Cholesterol test if not available     | +                                             |                                                                |
| Laboratory documentation              | +                                             | +                                                              |
| Qualitative research (sample)         |                                               | +                                                              |

See Appendix 1 for collected variables in each questionnaire/eCRF

#### Collection of variables

The primary source of information will be the patient's medical record. Baseline data elements to be abstracted and entered include patient demographics, medical history, patient FH history and diagnosis, FH type, family history, physical examination findings including blood pressure and physical signs of lipid accumulation in the tissue, current lipid-lowering therapies and laboratory values. A list of variable collected is found in the **Appendix 1**.

#### Laboratory documentation

The most recent laboratory measurement will be collected for lipids according to **Appendix 1**.

## 4.4 Withdrawal and discontinuation

Participants may withdraw from the study at any time at their own request, or they may be withdrawn at any time at the discretion of the investigator for safety or behavioral reasons, or the inability of the subject to comply with the protocol required schedule of study visits or procedures.

Participants who refuse to submit a questionnaire will remain in the study and will continue to be followed for protocol specified follow-up procedures. The only exceptions to this are when a participant specifically withdraws consent for any further contact with him/her or persons previously authorized by subject to provide this information. Medical data and biological material (blood samples, tissues, etc.) collected so far will still be analysed, so as not to compromise the value of the study as a whole. After the analysis, data and biological material will be made anonymous by permanently erasing the code linking to identifiers.

If a participant does not return for a scheduled visit, every effort should be made to contact him, to reschedule the visit, by phone, e-mail, text message, and if necessary, by letter and/or certified mail. All reasonable efforts must be made to locate participants to determine and report their ongoing status. This includes follow-up with persons authorized by the participants.

Lost to follow-up is defined by the inability to reach the participant after a minimum of three documented phone calls, faxes, or emails as well as lack of response by participant to one registered mail letter. Additional attempts to contact the participant may be performed, until the study is completed.

## **5 STATISTICS AND METHODOLOGY**

### **5.1. Statistical analysis plan and sample size calculation**

The sample size has been calculated according to the primary outcome, for each of the study groups, monogenic *positive* and *negative* FH. The statistician team of Unisanté ([name] and [name]) has estimated the sample size.

The aim of the study is to show that the proportion of people who agree to do the screening is higher in the experimental group than in the control group. Consents and refusals being measured within the families, the observations are not independent. Thus, it would be inappropriate to compare the consent rates of the control and experimental groups using a chi-square test. To account for the effect of clusters, proportions will be compared using an odds ratio that will be estimated using a logistic regression model. The latter will include the group as a fixed effect (the parameter of interest) and the family as a random effect.

For the monogenic *positive* FH group, we calculated that it will be necessary to include 41 families per group to show a statistically significant difference between the two groups with a significance level of 5% and a power of 90%, assuming that the consent rates for the control and interventional groups will be in mean equal to 0.15 respectively 0.3 and will be at 95% in the intervals [0.1,0.2] (range 0.05) respectively [0.1,0.5] (range 0.2) and that the number of contactable relatives will be in mean equal to 4.

For the monogenic *negative* FH group, we calculated that it will be necessary to include 36 families per group to show a statistically significant difference between the two groups with a significance level of 5% and a power of 90%, assuming that the consent rates for the control and interventional groups will be in mean equal to 0.5 respectively 0.7 and will be at 95% in the intervals [0.30,0.70] (range 0.4) respectively [0.46,0.86] (range 0.4) and that the number of contactable relatives will be in mean equal to 4.

These sample sizes were calculated analytically based on the standard errors of the mean proportions and were verified using simulations.

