## Summary of changes between final and original statistical analysis plan from protocol

### V1.3, dated 10.08.2022

#### Sample size:

The sample size calculation originally described in the protocol V1.3, dated 10.08.2022 was slightly revised as follows . The revised calculation assumed an intraclass correlation coefficient of 0.2 to account for family effects. This translates into 95% prediction intervals for family-specific participation probabilities of 9 - 22% in the control arm, and 20 - 41% in the intervention arm. With these adjustment, the required sample size increased to 44 families per arm (vs 41 in the protocol V1.3, dated 10.08.2022).

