| Study Design                   | Multicenter open-label randomized controlled trial, with 2x 2 arms. Index cases with clinical criteria for FH will be separated into two groups before randomization, based on the result of the genetic test, either positive or negative for a monogenic mutation in one of the three genes causing FH. In each of these two groups, a randomization procedure will allocate index cases and their family member into the intervention arm or the control arm to evaluate the best method to contact at-risk relatives and perform cascade screening. In the intervention arm, the index case will be actively supported by a web-based centralized service to initiate contact with their first-degree relatives. In the control arm or "usual care arm", the index case will be encouraged to initiated contact with their first-degree relatives, but without additional support. The presence or absence of a monogenic mutation in the index case will determine the screening test used for cascade screening of relatives, either genetic or lipid test. |
| Statistical Considerations     | The sample size has been calculated according to the primary outcome, for each of the study groups, monogenic positive and negative FH. For the monogenic positive/negative FH group, we calculated that it will be necessary to include 41/36 families per arm to show a statistically significant difference of 20% in the consent rate between the control and interventional arm. These sample sizes were calculated analytically based on the standard errors of the mean proportions and were verified using simulations by the statistician team of Unisanté.                                                                                                                                                                                                                                                                                                                                                                                                                                                                         |

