#### *Inclusion-exclusion criteria for relatives of an index case*

The study will recruit adults and children age  $\geq 5$  years in the cascade screening programme, who are relatives of the index case.

Inclusion criteria of the relatives include:

- Age  $\geq 5$  years old
- To be a first-degree relative of an index case included in the study
- Ability to give informed consent as documented by signature; children younger than 16 years will be enrolled only with the explicit consent of a parent or legal guardian

Exclusion criteria of the relatives include:

- Living outside Switzerland, except if they are leaving close to the border and a medical visit to one of the study center would be feasible
- Pregnant or lactating women, because cholesterol values are not interpretable during pregnancy.
- Inability to follow the procedures of the study, e.g. due to language problems, psychological disorders, dementia. (having an email address is not mandatory for relatives)

We will include 82 index cases with monogenic *positive* FH, as well as 72 index cases with monogenic *negative* FH, for a total of 154 index case. Furthermore, we assume that about 250 patients with clinical criteria of FH will need to be screened to identify 82 index cases with monogenic *positive* FH. Out of the about 200 patients with monogenic *negative* FH, the first 72 will be included. Therefore, about 130 patients with monogenic *negative* FH will not be proposed for cascade screening within this study once the sample size has been achieved.

In the two intervention groups, we estimate that four relatives per index case will participate to the screening programme. In the two control groups, we estimated that two relative per index case will contact the study center for cascade screening. Thus we plan to include a total of about 400 participants in the study, including relatives.

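### In protocol section 5.1 the stated 95% intervals for family consent rates need 44–45 families per arm for 90% power, and the stated 41 gives about 88%

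*Combined protocol and SAP*

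**What the plan says.** Protocol V1.3, section 5.1, sizes each genetic group separately at a "significance level of 5% and a power of 90"%, with four contactable relatives per family on average. It states that the sizes were derived analytically from the standard errors of the mean proportions and then checked by simulation. No formula is printed.

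- **Monogenic-positive group:** consent rates "in mean equal to 0.15 respectively 0.3", with 95% of family rates in the "intervals [0.1,0.2] (range 0.05) respectively [0.1,0.5] (range 0.2"). Result: 41 families per group.
- **Monogenic-negative group:** mean rates 0.5 and 0.7, with family rates in the "intervals [0.30,0.70] (range 0.4) respectively [0.46,0.86] (range 0.4"). Result: 36 families per group.

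The synopsis repeats the sizes ("include 41/36 families per arm"), and section 4.1 turns 41 per arm into a recruitment figure ("We will include 82 index cases" with a positive test).

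The final SAP, in its summary of changes under Sample size, revises the calculation. It assumes an intraclass correlation of 0.2, gives new family-level intervals of 9–22% and 20–41%, and reports that "the required sample size increased to 44 families per arm".

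**The concern.** The word *range* has two meanings in adjacent paragraphs of one calculation. For the negative group it is the full width of the interval: 0.70 − 0.30 = 0.4 and 0.86 − 0.46 = 0.4. For the positive group it is the half-width: 0.2 − 0.1 = 0.1 but 0.05 is printed, and 0.5 − 0.1 = 0.4 but 0.2 is printed.

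If the printed ranges had only been mislabelled, nothing would follow. If they were entered in the formula as full widths, the between-family SD for the positive group was halved and its variance quartered. The number of families would then be too small for the assumptions printed beside it. At stake is whether 41 families per arm and 90% power belong together, and whether a reader can rebuild the size from the stated assumptions.

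**Working it through.** **Inputs (section 5.1).** Two-sided α = 0.05 (sidedness is not stated; two-sided is assumed), power 0.90, four relatives per family (taken as fixed), and the means and intervals above.

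**Formula.** The usual normal approximation for a difference in mean family proportions, which fits the protocol's description of its method:

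n per arm = (1.960 + 1.2816)² × [p₀(1−p₀)/4 + s₀² + p₁(1−p₁)/4 + s₁²] / (p₁−p₀)², with s = full interval width / 3.92 and (1.960 + 1.2816)² = 10.507.

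This is the additive form. The exact form multiplies each s² by 3/4, because the binomial term should be (p(1−p) − s²)/4.

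**Step 1: reproduce the stated sizes from the printed ranges, read as full widths.**

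- Negative group: binomial terms 0.0625 + 0.0525 = 0.1150. s = 0.4/3.92 = 0.1020, so the two s² add 0.0208. n = 10.507 × 0.1358 / 0.04 = 35.7, so **36** (stated 36). The exact form gives 34.3, so 35.
- Positive group: binomial terms 0.0319 + 0.0525 = 0.0844. s₀ = 0.05/3.92 = 0.0128 and s₁ = 0.2/3.92 = 0.0510, adding 0.0028. n = 10.507 × 0.0871 / 0.0225 = 40.7, so **41** (stated 41). The exact form gives 40.4, so 41.

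**Step 2: use the positive-group intervals as stated (widths 0.1 and 0.4).** s₀ = 0.1/3.92 = 0.0255 and s₁ = 0.4/3.92 = 0.1020.

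- Additive: the sum is 0.0844 + 0.0111 = 0.0954. n = 10.507 × 0.0954 / 0.0225 = 44.6, so **45**.
- Exact: the sum is 0.0844 + 0.0083 = 0.0927. n = 43.3, so **44**.

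**Step 3: power under the stated intervals**, as Φ(0.15/√(sum/n) − 1.960).

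| Families per arm | Additive | Exact |
|---|---|---|
| 41 | 87.5% | 88.4% |
| 44 | 89.6% | 90.5% |

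For 41 additive: √(0.0954/41) = 0.0482, 0.15/0.0482 = 3.11, and Φ(1.15) = 0.875.

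Beta-binomial simulations with four relatives per family agree. At 41 per arm, one set of 40,000 runs gave 87.5–88.1% across three test statistics, and another of 20,000 runs gave 88.8% for a robust Wald test on the log-odds scale. At 44 per arm they gave 90.0–90.5% and 91.0%. With family size varying around four, 41 per arm gave 87.4–88.0%. A t-based version of the formula is slightly worse: 45–46 families needed, and 86.7–87.6% at 41.

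**Step 4: alternative explanations of 41.**

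- *Range* as half-width in both groups: the negative group would need 47–53 families, not 36.
- No clustering: a standard two-proportion formula gives 161 relatives per arm, and 161/4 = 40.25, so 41. The negative group would then need 31, not 36.
- One-sided test: about 35–37 families for the positive group under the stated intervals, and 33–34 under the halved ones.

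Of the readings tried, only *range* as full width in both paragraphs gives both 41 and 36.

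**The case against.** The strongest reply is that 41 no longer governs the trial. The final SAP replaces it with 44 per arm, and the monogenic-negative trial was not carried out. Under the V1.3 intervals 44 gives about 90% power, so nothing in the conduct of the trial turns on this. That stands and sets the weight of the point.

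A second reply is that the cause is inferred. The match to 36 needs the additive form, since the exact form gives 35. The interval [0.46, 0.86] has midpoint 0.66 and not 0.7; its logit-scale centre is 0.696, so another scale may have been used. This also stands: that halved intervals were used is a likely explanation, not a documented fact. The inconsistent labels and the shortfall at 41 do not depend on it.

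A third reply is that the loss is small, at 1.2 to 2.5 points, and that uncertainty in the assumed rates could matter as much. This is fair, but it does not make 41 and 90% consistent with the stated assumptions.

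A reader might also infer that the SAP's reason for moving from 41 to 44 is wrong, because the V1.3 intervals already required 44–45. The documents do not support that. The SAP presents a revision under new assumptions and correctly reports the two figures. For its intervals (widths 0.13 and 0.21) the formula above gives 40.8–41.3, so 41–42 families and not 44. The formula therefore does not show how 44 was obtained, and its closeness to the 44–45 found here may be coincidence.

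**Conclusion.** The point holds as a minor arithmetic inconsistency in protocol section 5.1. The positive-group ranges contradict the intervals they describe. Under those intervals 90% power needs 44 families per arm (exact form) or 45 (additive form), and 41 per arm gives about 88% (87.5–88.8%).

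This rests on a two-sided 5% test, four relatives per family, the stated mean rates, and a between-family SD of interval width/3.92. Varying family size or a t reference lowers the power at 41 slightly further.

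It would be wrong to conclude that the trial as finally planned falls short on this account: 44 per arm gives 89.6–90.5% by formula under the same intervals. Whether the SAP's correlation of 0.2 fits its own intervals is a separate question, not settled here.

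**What to change.** In section 5.1, change the positive-group ranges to 0.1 and 0.4, so that the word means full width throughout. Then state one of two things:

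- 44–45 families per arm for 90% power, naming the variance formula that decides between them; or
- 41 families per arm with about 88% power.

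Carry the choice to the synopsis and section 4.1. Under the first option the positive-group total becomes 88–90 index cases (2 × 44 or 2 × 45) in place of 82. Under the second, 82 stays and only the power statement changes.

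Optionally, add a sentence to the SAP's summary of changes: the V1.3 intervals as stated already called for about 44–45 families per arm, so the 44 now adopted gives about 90% power under them too. The SAP's stated reason for the revision can remain.

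The cost is a few words and one restated figure, with a slightly less favourable power at 41. No recruitment or analysis change is needed.
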